## Methods and design

### Participants

Patients with stroke who meet the following criteria will be recruited: (1) ≥ 3 months’ onset from a first-ever unilateral stroke, (2) age range from 18 to 80 years, (3) baseline UE motor score on the Fugl-Meyer Assessment (FMA) > 10 [18], (4) no severe spasticity in any joints of the affected arm (Modified Ashworth Scale ≤ 3) [19], (5) able to follow study instructions (Mini-Mental State Examination Score ≥ 24) [20], (6) no serious vision deficits or other neurologic or major orthopedic diseases, (7) able to participate in a rehabilitation intervention program for 6 weeks, and (8) no participation in other studies during the study period and willing to provide written informed consent. Exclusion criteria are (1) acute inflammation, (2) major medical problems or poor physical condition that might interfere with participation, and (3) simultaneously participating in other medication or rehabilitation studies during the trial. However, the patients may continue relevant concomitant care and interventions such as standard physical therapy or taking needed medications.

### Sample size estimation

No published research to date has compared the effects of bilateral RT+MT, RT+BAT, and RT+impairment-oriented training (IOT). Thus, the sample size required for this project was calculated and estimated based on our published studies [8, 21, 22].

In a previous study, we randomized 21 stroke patients to two treatments: RT+task-oriented training and RT+IOT [21]. Between-group analyses revealed small to large effects on the FMA (*p* = 0.01, *η*^2^ = 0.43), Stroke Impact Scale (*p* = 0.046, *η*^2^ = 0.29), and Medical Research Council scale (*p* = 0.98, *η*^2^ < 0.01), respectively.

An additional 21 stroke patients were randomized to receive RT+BAT or RT [8]. Between-group analyses revealed small to large effects on the FMA (*p* = 0.82, *η*^2^ = 0.003) and Goal Attainment Scale total scores (*p* > 0.01, *η*^2^ = 0.633). We randomized 23 stroke patients to two treatment groups: MT and BAT [22]. Between-group analyses revealed small to large effects on the FMA (*p* = 0.67, *η*^2^ = 0.009) and Stroke Impact Scale Version 3.0 total scores (*p* = 0.02, *η*^2^ = 0.165), respectively.

In addition, we used the pilot data of three groups for the FMA proximal UE score (*p* = 0.051, *η*^2^ = .114) to calculate sample size. In light of our previous findings [8, 21, 22], we estimate that to achieve a statistical power of 0.80 with a two-sided type I error of 0.05 and with an estimated dropout rate of 10% to 15% at the 3-month follow-up, a total sample size of 96 with 32 subjects for each group will be sufficient.

### Design and procedure

This study is a single-blind, randomized controlled trial with pretest, posttest, and 3-month follow-up assessments. This comparative efficacy study will be based on a controlled trial with 3 arms: bilateral RT+MT, bilateral RT+BAT, and the control intervention of bilateral RT+IOT. The randomization sequence will be created by using a random number table with an allocation ratio of 1:1:1. Participants will be recruited from four study sites (i.e., National Taiwan University Hospital in Taipei, Chang Gung Memorial Hospital in Linkou, Taipei Hospital in New Taipei City, and Taipei Tzuchi Hospital in New Taipei City). Our therapists will screen eligible participants every day at each study site. When new participants are registered, a blinded research assistant will prepare a sheet containing the assigned group of the participants in a sealed envelope and give it to the therapist. A total of 96 eligible subjects will be stratified into four strata according to the side of lesion (right-side vs. left-side cerebrovascular accident) and the level of motor impairment (the cutoff will be 33 points on the FMA- UE Subscale) [23] at each of the four study sites to balance randomization assignment (4 strata with 24 subjects at each site). However, unblinding of participant’s group assignment is permissible when knowledge of the actual treatment is absolutely essential for further management of the patient.

The Ethical Committees for Human Research at the hospitals where participants are recruited have approved the study protocol. A well-trained and certified occupational therapist, who is blinded to the group assignment, study hypotheses, and intervention of the patients, will administer baseline, postintervention, and 3-month follow-up assessments. The baseline assessment will take place within 1 week before the start of the intervention, and the postintervention assessment within 1 week after the end of the intervention. Table 1 presents the timing of all study procedures.

**Table 1 Tab1:**
[figure not shown]
The schedule of enrolment, interventions, and assessments of this study protocol

### Intervention

Each treatment session will be delivered one-on-one by licensed occupational therapists. The Bi-Manu-Track robot (Reha-Stim Co., Berlin, Germany) will be used for the RT for 40 to 45 min in the three groups. Participants will sit at a height-adjustable table and practice 2 mirror-like movements: forearm pronation-supination and wrist flexion-extension with three computer-controlled modes: (1) passive-passive, with both arms being moved by the machine; (2) active-passive, with the unaffected arm driving the affected arm in a mirror-like fashion; and (3) active-active, with both arms actively moving against resistance. The speed of movement, the amount of resistance, and the range of movement can be adjusted individually on the Bi-Manu-Track. Computer games will be used to provide visual feedbacks to facilitate participation and motivation during the RT session. Participants are expected to perform approximately 1200 to 1600 repetitions of movements as bilateral robotic priming.

#### Experimental group 1: Bilateral robotic priming to be combined with bilateral arm training (RT+BAT)

After the robotic priming, participants will receive another 40 to 45 min of training in tasks focusing on bilateral symmetric movements of both UEs. The therapist will encourage the participants to perform the task with their paretic UEs as symmetrically as possible. The activities performed by the participant may involve 5-min intransitive movements (e.g., elbow flexion/extension or forearm pronation/supination) and 35 to 40 min of transitive tasks (e.g., flipping cards, scooping soup out of a bowl, or wiping the table), depending on the level of UE function. The tasks will be selected and graded on an individual basis to fit into the participants’ personal need for functional recovery.

#### Experimental group 2: Bilateral robotic priming to be combined with mirror therapy (RT+MT)

After bilateral robotic priming, participants will receive 40 to 45 min of MT. During MT, a wooden mirror box (41 × 50 × 33 cm^3^) will be placed in front of the participant to block the participant’s view of the paretic UE performance. The participants will be asked to use their less paretic UE to perform certain functional tasks and to observe the less paretic UE movements reflected from the mirror. Simultaneously, the therapist will encourage the participant to perform the task as symmetrically as possible with the paretic UE behind the mirror. The MT protocol will be similar to that of BAT except for the use of mirror feedback in MT. The activities and tasks performed by the participant will depend on the level of UE function and the participant’s personal need for recovery.

#### Control intervention group: Bilateral robotic priming to be combined with impairment-oriented training (RT+IOT)

IOT is an approach developed to restore body functions after stroke, including remediation of motor impairments, rather than restoring functional performance [24]. Since motor impairments are prevalent in patients with stroke, IOT is a common approach in stroke rehabilitation. Therefore, we chose RT+IOT as the control intervention group in this study.

After bilateral robotic priming, participants will receive 40 to 45 min of IOT. Participants in the control group will receive systematic repetitive training, the Arm Basis Training or the Arm Ability Training, according to each participant’s impairment level. Participants with a baseline FMA-UE score lower than 35 or without the ability of a precision grip will receive the Arm Basis Training, whereas participants with a baseline FMA-UE score of 35 or more and the ability of a precision grip will receive the Arm Ability Training.

The Arm Basis Training protocol will focus on the capacity of selective movements in all arm segments (shoulder, elbow, forearm, wrist, and fingers), from isolated movements without weight bearing of the affected UE to the movements against and with gravity and from single-joint motions to multiple-joint motions. The Arm Ability Training targets different sensorimotor abilities, such as speed, grasping, aiming, dexterity, tracking, steadiness, accuracy, and endurance with eight training activities (aiming, tapping, cancelation, turning coins, maze tracking, bolt and nut, placing small objects, and placing large objects) [21, 24, 25]. Table 2 summarizes the treatment regimen for the experimental and control groups.

**Table 2 Tab2:** Treatment regimen for the experimental and control groups

Group	Treatment	Duration	Frequency	Intensity
Experimental 1	Bilateral RT+BAT	90 min/day 45 min: RT 45 min: BAT	3 days/week	6 weeks
Experimental 2	Bilateral RT+MT	90 min/day 45 min: RT 45 min: MT	3 days/week	6 weeks
Control	Bilateral RT+IOT	90 min/day 45 min: RT 45 min: IOT	3 days/week	6 weeks

*RT* Robotic therapy, *BAT* Bilateral arm training, *MT* Mirror therapy, *IOT* Impairment-oriented training

### Outcome measures

#### Primary outcome measurement

##### Fugl-Meyer Assessment (FMA)

The UE subscale of the FMA will be used to assess motor impairment [18]. There are 33 UE items measuring the movements and reflexes of the shoulder/elbow/forearm, wrist, hand, and coordination/speed. Each score is on a 3-point ordinal scale (0 = cannot perform, 1 = performs partially, 2 = performs fully), with a maximum score of 66 as optimal recovery. The subscale score of a proximal shoulder/elbow (FMA s/e: 0–42) and a distal hand/wrist (FMA h/w: 0–24) will be calculated to investigate the treatment effects on separate UE elements. The FMA has good reliability, validity, and responsiveness in stroke patients [26].

#### Secondary outcome measurements

##### Stroke Impact Scale Version 3.0

The Stroke Impact Scale Version 3.0 is a stroke-specific health-related quality of life instrument (Duncan et al., 2003). It consists of 59 items assessing eight domains: strength, hand function, activities of daily living/instrumental activities of daily living, mobility, communication, emotion, memory, thinking, and participation. Items are rated on a 5-point Likert scale, with lower scores indicating greater difficulty in task completion during the past week. The Stroke Impact Scale Version 3.0 has satisfactory reliability, validity, and responsiveness in stroke patients [27].

##### Medical Research Council scale

The Medical Research Council scale will be used to measure muscle strength of UE joints of the affected arm by the 6-point ordinal scale (0 = plegic, 5 = resisted to maximal strength, full power compared with the unaffected side), and the average Medical Research Council scale score will be calculated. The Medical Research Council scale demonstrates reliability in muscle power measurement [28].

##### Revised Nottingham Sensory Assessment

The Revised Nottingham Sensory Assessment will be used to evaluate changes in sensation, including tactile sensation, proprioception, and stereognosis of different segments of the body [29]. The Revised Nottingham Sensory Assessment is scored on a 3-point ordinal scale (0–2), with a lower score suggesting greater sensory impairment. The psychometric properties have been established for patients with stroke [29].

The *ABILHAND Questionnaire* is an inventory of 23 manual activities on which the patient provides his or her self-perceived performing difficulty on a 4-level scale (0 impossible, 1 great difficulty, 2 some difficulty, 3 easy) [30]. Its reliability and construct validity has been confirmed in stroke patients [30].

The *Goal Attainment Scale* is an individualized outcome measure of the achievement of each participant’s expectation in the course of the intervention. The goals will be set before the intervention and scored the day before the treatment (pretest), after 6 weeks of treatment (posttest), and follow-up.

The *Functional Independence Measure* is an 18-item measurement tool that assesses a patient’s self-care, sphincter control, transfer, locomotion, communication, and social cognition ability [31], with a higher score (maximum score, 126) indicating less disability. The Functional Independence Measure has good inter-rater reliability, construct validity, and discriminant validity [31].

The *Stroke Self-Efficacy Questionnaire* is a 13-item questionnaire that measures a participant’s confidence in functional performance from stroke, rated from 0 (no confidence at all) to 10 (complete confidence). A higher score (maximum score, 130) indicates higher self-efficacy in functional performance from stroke. The Stroke Self-Efficacy Questionnaire has high internal consistency and good criterion validity [32].

The *Actigraphy* is an ActiGraph GX3 accelerometer (ActiGraph, Shalimar, FL, USA) that is worn on the wrist and may record activity levels of the patient’s UE for 3 consecutive days before and after the intervention. The accelerometer will record the number of moves each minute, and the average counts of moves per minute will be calculated.

##### Myoton Pro

The functional state of skeletal muscle, that is, muscle tone, elasticity, and stiffness, will be objectively assessed by the Myoton Pro (Muomeetria Ltd, Tallinn, Estonia) device after interventions.

##### Adherence

The following strategies will be implemented to increase participants’ adherence and retention to this study. Transportation is provided to participants to and from home to the study sites. Therapists will make a phone call to each participant every week and visit the participants at home as need. Participant’s adherence will be measured based on session attended and completed.

##### Data management and quality

All documents in this study will be stored in a locked cabinet, including signed informed consent forms and data recording sheets. The electronic database will be protected by using a password. No identifiable personal information of the participants will be available from the electronic database. The principle investigator ([name]) was in charge of data monitoring in this study. Therefore, there was no additional data monitoring committee. The second author of this study ([name]) will conduct interim data analyses and the principle investigator ([name]) will make the final decision to terminate the trial.

##### Adverse event monitoring and reporting

The vertical numerical rating scale supplemented with a faces rating scale [33] and a self-reported assessment will be provided to evaluate adverse effects on fatigue and pain severity, respectively. Both assessments, using 11-point scale (0 = no fatigue/pain to 10 = worst possible fatigue/pain), will be applied after each training session and at 3 months in the follow-up period. The therapist may adjust the practice activities based on the participant’s self-perceived burdens. The reliability and validity of the vertical numerical rating scale supplemented with a faces rating scale in measuring fatigue intensity in patients with stroke are supported by previous study [33]. In addition to pain and fatigue, other adverse events will be monitored and reported, including fall, seizure, dizziness, and hypertension.

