**Methods:**

This single-blind, randomized, comparative efficacy study will involve 96 participants with chronic stroke. Participants will be randomized into bilateral RT+MT, bilateral RT+BAT, and bilateral RT+IOT groups and receive 18 intervention sessions (90 min/day, 3 d/week for 6 weeks). The outcomes will include the Fugl-Meyer Assessment, Stroke Impact Scale version 3.0, Medical Research Council scale, Revised Nottingham Sensory Assessment, ABILHAND Questionnaire, and accelerometer and will be assessed at baseline, after treatment, and at the 3-month follow-up. Analysis of covariance and the chi-square automatic interaction detector method will be used to examine the comparative efficacy and predictors of outcome, respectively, after bilateral RT+MT, bilateral RT+BAT, and bilateral RT+IOT.

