### Statistical analyses

One-way analysis of variance and *χ*^2^ will be used to analyze differences in baseline characteristics and outcome measures among the three groups. Analysis of covariance will be conducted at the assessments, followed by a post hoc analysis using the Bonferroni test to identify the direction of the effects. Statistical significance will be set at 0.05 for all comparisons. We will use the “pretest” performance as a covariate to parcel out the possible confounding effects of differences in baseline performance. The group will be the independent variable and the posttest and follow-up test performance will be the dependent variable. The missing data will be adjusted based on the last observation carried forward (Herman, 2009). Partial eta squared (*η*^2^) will also be estimated to determine the group difference for each outcome measure. Predictors of intervention outcomes will be estimated with the chi-square automatic interaction detector method. Data analyses will be performed using the SPSS Statistics 18.0 software (IBM Corp, Armonk, NY).

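### Pain and fatigue are rated only after training sessions and at 3 months, so symptom-driven absence goes unrated and some safety summaries may understate the burden of a less tolerable regimen

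*Protocol article*

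**What the plan says.** In the protocol article, the section on adverse event monitoring and reporting sets the occasions for the two self-reported 0 to 10 scales: they "will be applied after each training session and at 3 months in the follow-up period". It adds: "In addition to pain and fatigue, other adverse events will be monitored and reported, including fall, seizure, dizziness, and hypertension". That sentence is not tied to attendance.

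The Adherence section provides contact outside sessions: "Therapists will make a phone call to each participant every week and visit the participants at home as need". It presents this as a way to improve adherence and retention, and does not say that symptoms or reasons for absence are asked about. It continues: "Participant’s adherence will be measured based on session attended and completed".

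The sample size section plans "with an estimated dropout rate of 10% to 15% at the 3-month follow-up". The Statistical analyses section states "The missing data will be adjusted based on the last observation carried forward", without saying whether this covers the pain and fatigue ratings. The Design and procedure section places the posttest within 1 week after treatment ends.

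**The concern.** Under this schedule a rating during the treatment period exists only if the patient came to train. Pain and fatigue are the two effects the article chose to measure by scale, and both are plausible reasons for missing a 90-minute session or stopping. Whether a score exists can therefore depend on the score itself, which is informative missingness created by the collection rule.

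There is a second, smaller gap. By the text, a patient who completes training is rated after session 18 and next at 3 months. A symptom that appears in the days after the last session and settles before 3 months has no stated rating, although a posttest visit falls in that window.

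What is at stake is the tolerability comparison between the three regimens. The primary Fugl-Meyer analysis is not affected. A score that was never collected cannot be recovered by an analysis plan.

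**Working it through.** The article gives no figure for pain or fatigue, so there is nothing to reproduce. The check sets out what the schedule collects, then asks how far different summaries could be distorted.

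**1. Rating occasions.** 18 sessions + 1 follow-up = at most 19 per patient. A patient whose last session is number 6 contributes 6, plus one at 3 months if they return.

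**2. How many could be affected.** 10% to 15% of 96 is 9.6 to 14.4 patients; of 32 it is 3.2 to 4.8 per arm. This is total dropout at 3 months. The article does not say how many leave during treatment, or why.

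**3. One arm by hand (all scores assumed).** Of 32 patients, 3 have pain 7 throughout and stop after session 6. The other 29 have pain 2 and attend all 18 sessions.

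- Mean if everyone were rated every time: (3×7 + 29×2)/32 = 79/32 = 2.47.
- Last-session mean among attenders: 2.0, which is 0.47 too low.
- Pooled session scores: (3×6×7 + 29×18×2)/(3×6 + 29×18) = 1170/540 = 2.17, which is 0.30 too low.
- Mean of patient means: (3×7 + 29×2)/32 = 2.47, no bias.
- Last observation carried forward: 2.47, no bias, but only because the score was assumed constant after leaving.
- Share with 7 or more at any time: 3/32 = 9.4%, fully recorded, because those patients were rated after session 6. Counted at the last session only, it is 0/29.

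The distortion therefore depends on the summary used, which the article does not fix.

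**4. Two arms by simulation (all inputs assumed).** There were 20,000 patients per arm and 18 sessions, with mean scores of 3 and 4, between-patient SD 1.5 and within-patient SD 1.2. Scores were rounded and limited to 0 to 10. After a score of 6 or more, the patient may miss the next session or withdraw. Entries are the difference, worse arm minus milder arm.

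| Miss next / withdraw | Withdrawn, milder / worse arm | All sessions, complete data | Pooled observed | Last session, complete data | Last session, attenders | Patient means | Last carried forward |
|---|---|---|---|---|---|---|---|
| 30% / 2% | 3% / 6% | 0.96 | 0.90 | 0.96 | 0.88 | 0.97 | 1.02 |
| 50% / 5% | 6% / 12% | 0.95 | 0.84 | 0.94 | 0.78 | 0.96 | 1.03 |
| 50% / 15% | 16% / 29% | 0.95 | 0.79 | 0.96 | 0.72 | 0.98 | 1.11 |

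The pooled difference falls by 0.06/0.96 = 6% to 0.16/0.95 = 17%. The last-session difference falls by 0.08/0.96 = 8% to 0.24/0.96 = 25%. The worst observed score falls less: 1.00 to 0.97, 0.98 to 0.92 and 0.99 to 0.88. The difference in the share ever scoring 6 or more is 0.24 with or without the missing ratings.

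Two limits apply. The last row loses more patients in both arms than the article's 10% to 15%, so the first two rows are the more relevant. Also, absence was made to follow a rated high score, so the unchanged 0.24 is partly built in: a symptom that first becomes severe after the last attended session would be missed under every summary.

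**The case against.** A reader might infer that a patient who leaves because of pain disappears from the safety data, and that the worse regimen will therefore look better tolerated. The documents do not support that. Every rating up to withdrawal is kept, including a high one just before leaving. The text asks for a rating after each session without requiring that the session be completed. The 3-month rating is not conditional on finishing treatment. No between-arm analysis of pain or fatigue is described, so no biased comparison is specified. Bias also needs absence that is driven by symptoms and differs by arm, for which the article gives no evidence. If the carry-forward rule covers these ratings, a high last score is retained. No simulated scenario reversed the arms.

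Other routes exist too. Other adverse events are followed without a stated link to attendance, every participant is phoned weekly, and attendance is counted, so absence by arm will be visible. Table 1 may list ratings at posttest, and the full protocol may record reasons for withdrawal.

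All of this stands, and it limits the point to a possible understatement under some summaries. It does not remove the gap. The rating schedule is stated, and it includes nothing for absent patients. A count of missed sessions does not say why they were missed. Carrying a score forward repeats an old rating; it does not record what happened after the patient stopped.

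**Conclusion.** The point holds in a limited form. By the stated text, no pain or fatigue rating is planned for missed sessions or at withdrawal, and none is stated for posttest, subject to the unseen Table 1. If absence is symptom-driven and differs between arms, pooled or last-session scores may understate the burden of the less tolerable regimen. The real size is unknown. Under the assumed inputs the arm difference was reduced by 6% to 17% (pooled) and 8% to 25% (last session), and the upper ends come from a scenario with more withdrawal than the article expects. Patient means and any-time counts were close to unaffected, and carrying forward enlarged the difference slightly. A reversal is not shown. This is a worthwhile, low-cost improvement in data collection. It is not a threat to the trial's main conclusion, and since recruitment was open at submission it could still help later participants.

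**What to change.** In the weekly call, ask every randomised participant, including those who missed sessions or stopped training, for the two 0 to 10 ratings and the reason for any missed session or withdrawal. Add both ratings at the posttest visit, or confirm that Table 1 already includes them. Report per arm, over all randomised patients, the worst score at any time and the number of withdrawals due to pain or fatigue.

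The cost is a few scripted questions in a call and a visit that already exist, plus one table. The drawback is comparability: phone ratings are verbal, without the faces scale, and are taken by therapists who are not stated to be blinded. Tabulate them separately from the post-session ratings.
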